## Abstract

**Background:**

Adolescent and young adult use of electronic nicotine delivery systems (“vaping”) has increased rapidly since 2018. There is a dearth of evidence-based vaping cessation interventions for this vulnerable population. Social media use is common among young people, and smoking cessation groups on social media have shown efficacy in the past. The objective of this study is to describe the protocol for a randomized controlled trial (RCT) testing the efficacy of an Instagram-based vaping cessation intervention for adolescents and young adults.

**Methods:**

Adolescents and young adults aged 13–21 residing in California who have vaped at least once per week in the past 30 days will be recruited through social media ads, community partners, and youth serving organizations. Participants will be randomly assigned to intervention or control conditions: the intervention group takes place on Instagram, where participants receive up to 3 posts per weekday for 25 days over 5 weeks; the control group will be directed to kickitca.org, a website offering links to chatline and texting cessation services operated by the California Smokers' Helpline. The primary outcome is biochemically verified 7-day point prevalence abstinence for nicotine vaping; secondary outcomes are vaping reduction by 50% or more, vaping quit attempts, readiness to quit vaping, confidence in ability to quit, desire to quit, commitment to abstinence, and use of evidence-based cessation strategies. Both the primary outcome and secondary outcomes will be assessed immediately, 3 months, and 6 months after the treatment.

**Discussion:**

This is the first RCT to test a vaping cessation intervention delivered through Instagram. If effective, it will be one of the first evidence-based interventions to address vaping among adolescents and young adults and add to the evidence base for social media interventions for this population.

**Trial registration:**

ClinicalTrials.gov: NCT04707911, registered on January 13, 2021.

**Supplementary Information:**

The online version contains supplementary material available at 10.1186/s12889-022-14606-7.

## Background

The aggressive promotion and uptake of electronic nicotine delivery systems (colloquially called “vaping”) among youth in the US [1–9] have led to an increase in overall nicotine use [8, 10–13]. Among high school students, vaping increased 135% from 11.7% to 27.5% between 2017–2019 [8, 13]. Despite a documented decline in e-cigarette use among young people during the COVID-19 pandemic [14], in 2021, e-cigarettes continued to be the most commonly currently used tobacco product with 11.3% of high school students and 2.8% of middle school students reporting use in the past 30 days[15]. Vaping among young people is especially concerning because compared with older adults, the brains of adolescents and young adults are more vulnerable to the harmful health effects of nicotine that most e-cigarettes contain [16, 17]. In addition, e-cigarettes introduced in recent years have the potential to deliver equal or more nicotine compared to tobacco cigarettes [18], potentially increasing their addictiveness. Prevention programs to address adolescent vaping include prevention media campaigns and educational classroom materials, such as the Stanford Tobacco Prevention Toolkit [19] and the CATCH my breath e-cigarette educational program [20]. Fewer programs address vaping cessation for adolescents and young adults: telephone counseling and texting programs are offered [21, 22], and Truth Initiative offers a free texting vaping intervention that has shown efficacy in a randomized trial [23].

Social media have been a part of life for young Americans with 95% of adolescents and 84% of adults ages 18 to 29 ever using social media [24, 25]. While aggressive targeted marketing of e-cigarettes on social media such as Twitter, Instagram, and YouTube significantly contributes to high awareness of e-cigarettes and high e-cigarette use rates among youth [26, 27], social media are also a promising channel to reach a large number of adolescents and young adults who vape without geographical restrictions to deliver vaping cessation interventions. Social media-based smoking cessation interventions for adults have demonstrated feasibility, acceptability, and early efficacy [28, 29]. However, there are few effective and high-quality smoking cessation interventions for adolescents and young adults [30, 31] and even less evidence on social media interventions to address vaping. To the best of our knowledge, none of the existing vaping cessation interventions for adolescents and young adults are delivered via social media. To fill this gap, we will conduct a randomized controlled trial (RCT) to test the efficacy of a social media-based intervention designed specifically to support cessation among adolescents and young adults who vape. Though vaping cessation interventions are relatively new and rigorously tested programs are limited, a meta-analysis of research on adolescent cigarette smoking cessation interventions showed that cessation programs increased the probability of quitting by approximately 46%, with higher quit rates in programs that included a motivation enhancement component, cognitive-behavioral techniques, and social influence approaches [32]. This suggests that vaping inventions utilizing these strategies may be effective to address the problem of vaping among young populations. One model has incorporated Motivational Interviewing (MI), cognitive behavioral coping skills, and the Transtheoretical Model (TTM) of behavior change (i.e., readiness to quit) to create the Tobacco Status Project (TSP) [31, 33–35], a smoking cessation intervention for young adult smokers implemented entirely through private Facebook groups. Participants in TSP joined private Facebook groups where they received daily posts and were encouraged to interact with each other for 90 days [33]. Biochemically verified 7-day point prevalence abstinence at the 3-month follow-up was significantly higher in the intervention group (8.3%) compared to the control group referred to Smokefree.gov (3.2%) [33]. In our current study, we will deliver intervention materials adapted from TSP to address nicotine vaping, the adolescent and young adult target audience, and to deliver the program via the Instagram platform, which is more popular than Facebook among adolescents, being used by 72% of adolescents in 2018 [36].

## Objectives

This study will evaluate the efficacy of the Instagram-based vaping cessation intervention among adolescents and young adults in an RCT. The primary aim is to test the efficacy of the intervention to achieve biochemically verified nicotine vaping abstinence when the treatment ends and sustain it for 6 months after the treatment. The secondary aim is to test the effectiveness of the intervention in terms of decreasing vaping frequency, and increasing quit attempts, readiness to quit, confidence in ability to quit, desire to quit, commitment to abstinence, and use of evidence-based cessation strategies assessed immediately, 3 months, and 6 months after the treatment.

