### Sample size estimation

Power analyses were generated using the two-group repeated proportions module in NCSS PASS 14 [40] to compute minimum detectable effect sizes for the primary analysis. Assuming α = 0.05, power = 0.80, rho = 0.43 and a 7-day abstinence base rate of 3.2% and a quit rate of 8.3% in the treatment group from our preliminary data [31], group sample size of 234 (N_total_ = 468) is needed. Assuming a dropout rate of 7%, we need 500 participants.

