### Outcome measures

#### Primary outcome

7-day point prevalence abstinence will be assessed immediately, 3 months, and 6 months after the treatment. Participants reporting no nicotine vaping in the past 7 days will be coded as abstinent. At each follow-up assessment, those reporting 7-day abstinence and not using NRT will be mailed a saliva cotinine test kit for biochemical verification. Participants will be provided both written instruction and a video demonstrating how to correctly perform the saliva cotinine test, and take photos of themselves doing the test and a photo of the result, and how to send the photos to our research staff. Participants with a salivary cotinine level < 20 ng/ml will be considered to have achieved biochemically verified nicotine vaping abstinence.

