#### Primary analysis

We will use a generalized linear mixed model (GLMM) using the time points immediately, 3 months, and 6 months after the treatment. The model will account for dependence of responses within individuals attributable to repeated measures. GLMMs will include random effects person ID and will be fitted using SAS PROC GLIMMIX with maximum likelihood estimation via adaptive quadrature with a minimum of 15 integration points. Nicotine vaping abstinence will be measured by 7-day point prevalence. Covariates will be sex as a biological variable and other variables that are found to be related to abstinence. If missing data is not negligible, we will use multiple imputation procedures to impute missing data. Data about biochemically verified abstinence will be analyzed using the same method as self-reported 7-day point prevalence of abstinence.

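### The primary aim is abstinence sustained for 6 months, but the primary outcome is three separate 7-day snapshots, no end-of-treatment or 6-month contrast is named, and 234 per arm gives about 66% power at any one assessment

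*Protocol article*

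**What the plan says.** Objectives states the primary aim in two parts: the intervention is "to achieve biochemically verified nicotine vaping abstinence when the treatment ends and sustain it for 6 months after the treatment".

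The Primary outcome section defines something narrower: "7-day point prevalence abstinence will be assessed immediately, 3 months, and 6 months after the treatment", with saliva cotinine used to verify those who report abstinence. No sustained, prolonged or continuous abstinence outcome is defined.

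Primary analysis says "We will use a generalized linear mixed model (GLMM) using the time points immediately, 3 months, and 6 months after the treatment", that "GLMMs will include random effects person ID", and that "Nicotine vaping abstinence will be measured by 7-day point prevalence". Verified abstinence is to be analysed in the same way as self-reported abstinence. The section gives no primary time point, treatment-by-time term or contrast.

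Sample size estimation says "Power analyses were generated using the two-group repeated proportions module in NCSS PASS 14", with the inputs "Assuming α = 0.05, power = 0.80, rho = 0.43", 3.2% in control and 8.3% with intervention. The result is 234 per group (468 in total), raised to 500 for 7% dropout. The number of repeated measures is not stated. Background reports the same two percentages as the 3-month result of the earlier Facebook-based trial.

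**The concern.** The aim concerns what happens at treatment end and whether it lasts. The outcome records whether a participant was abstinent in each of three separate weeks. Different people may be abstinent at each one, and relapse between assessments goes unseen. Point prevalence at three times therefore does not measure whether anyone sustained abstinence.

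The sample size raises a second problem. A repeated-proportions calculation with a within-person correlation gains efficiency by combining assessments. The stated 80% power then belongs to a combined effect, whereas both parts of the aim rest on particular times: treatment end and 6 months. If the trial reports a significant combined effect, readers will want to know whether benefit remains at 6 months. The article names no test for that and has not powered one.

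**Working it through.** **Inputs (Sample size estimation).** p1 = 0.032, p2 = 0.083, alpha = 0.05 (sidedness not stated; two-sided assumed), power 0.80, rho = 0.43, n = 234 per arm.

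**Step 1: one assessment.** Two-proportion formula with pooled null variance:

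n = [1.96 × √(2 p̄(1−p̄)) + 0.842 × √(p1(1−p1) + p2(1−p2))]² / (p2−p1)²

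with p̄ = 0.0575. The two terms are 0.645 and 0.275, so n = (0.645 + 0.275)² / 0.051² ≈ 326 per arm. Other single-assessment formulas give 257 (one-sided) to 365 (continuity-corrected). None gives 234.

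**Step 2: reproduce 234.** Averaging M equally correlated measures multiplies n by (1 + (M−1)rho)/M.

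| M | Factor | n per arm | Power at 234 |
|---|---|---|---|
| 1 | 1 | 326 | 66% |
| 2 | 1.43/2 = 0.715 | 326 × 0.715 = 233.1, so 234 | 80% |
| 3 | 1.86/3 = 0.62 | 326 × 0.62 = 202.1, so 203 | 85% |

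Two measures reproduce the stated figure exactly. The closest three-measure variant, with continuity correction, gives 365 × 0.62 = 226.3, so 227.

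**Step 3: power at one assessment with 234 per arm.** z = [0.051 × √234 − 0.645] / √0.1071 = 0.41, so power is 66%. With 250 per arm, z = 0.49 and power is 69%. On the log-odds scale the figure at 234 is 63%. A one-sided test would give 77%.

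**Step 4: can an averaged effect show persistence?** Hold control at 3.2% throughout, with rho = 0.43 and 234 per arm, and test the difference in three-time averages (unpooled variance). The intervention rates are illustrative:
- Fading (13.3%, 8.3%, 3.2%): mean 8.27%, difference 5.07 points, SE 1.64 points, z = 3.08, power about 87%.
- Constant (8.3% at each time): difference 5.10 points, SE 1.68 points, z = 3.03, power about 86%.

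The averaged test is as likely to be positive when nothing is left at 6 months as when the benefit is fully kept.

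**Step 5: an outcome of abstinence at all three assessments.** This needs an assumed dependence structure, with 3.2% and 8.3% at each time and rho = 0.43.
- Beta-binomial: 0.88% against 2.51%, power 28% at 234 per arm, 982 per arm for 80%.
- First-order Markov: 0.64% against 1.89%, power 23%, 1,260 per arm for 80%.

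**The case against.** The strongest reply is that this is a condensed article and the analysis plan is not shown. A mixed model with a treatment-by-time term would yield both the end-of-treatment and the 6-month effects, and model terms are commonly left to the plan. That stands, and it rules out several stronger readings:

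- A reader might infer that the analysis pools the three times into one effect, or that treatment end goes untested. Primary analysis gives neither fixed effects nor a contrast, so the article supports only that no such test is specified.
- A reader might infer that the power holds only for the average of the three assessments. The figure of 234 matches two measures, and the number used is not stated.
- A reader might infer that an early-only effect would be declared to meet the aim. No success rule is stated.
- A reader might infer inflated error from testing each assessment at 5%. The article plans one longitudinal model and does not propose three separate tests.

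It can also be said that sustaining abstinence may mean persistence of the group-level difference. On that reading the 6-month arm difference carries the claim, and it is the contrast left unnamed and at about 66% power. Finally, Sample size estimation and Background cite different references for the two rates. The percentages are identical, so a common 3-month source is likely but not certain, and the power figures do not depend on it.

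The mismatch between aim and outcome survives all of this, because the article itself fixes both.

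**Conclusion.** The concern holds in this limited form. The primary aim includes sustained abstinence, the primary outcome does not measure it, and no contrast at treatment end or 6 months is named. The stated 80% power does not carry over to a single assessment, where 234 per arm gives about 66% and 250 gives about 69%; 80% would need 326 per arm. Nor does 234 fit the three planned measures, which need about 203.

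These figures assume a two-sided 5% test, the stated rates at the assessment in question, and, for the averages, equal correlation of 0.43 between assessments. The fading-effect comparison uses illustrative rates. It shows what an averaged test cannot separate and is no forecast of the trial. The point goes beyond missing detail because a positive averaged result would leave the second half of the aim unanswered.

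**What to change.** 1. Name one primary contrast, and restate its power with the number of repeated measures and the sidedness of the test.
2. If that contrast is the time-averaged effect, report the 6-month arm difference from the same model as the first-ranked secondary test, with its power of roughly 66% stated. Do not claim persistence from the averaged result alone.
3. Either reword the primary aim to point-prevalence abstinence at each time, or add verified abstinence at all three assessments as a supportive outcome. Describe the latter as repeated point prevalence, not continuous abstinence, and make no claim of sustained abstinence beyond it.

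The cost is wording and, at most, one variable derived from data already collected. The downside is that the 6-month result is openly lower-powered, and the all-three outcome has only about 23–28% power under the assumed dependence, so it can support the main result but not carry a conclusion of its own.

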## Methods/design

### Study design

This is an RCT with an intervention group and a control group. This study protocol was written according to SPIRIT (Standard Protocol Items: Recommendations for Interventional Trials), a guideline that defines standard protocol items for clinical trials and is widely endorsed as an international standard for trial protocols [37, 38]. The completed SPIRIT checklist is shown as Additional file 1.

### Participants

Adolescents and young adults aged 13–21 residing in California who have vaped at least once per week in the past 30 days will be recruited online via Facebook and other social media, augmented by outreach through community partners and youth serving organizations (the detailed recruitment procedure is elaborated in the Recruitment section below). This study focuses on adolescents and young adults aged 13–21 because people in this age group both need vaping cessation support and have integrated social media into daily life. Children under the age of 13 are not included because the intervention takes place on social media and popular sites all set their age limit at 13, in compliance with the Children’s Online Privacy Protection Act [39]. There are no exclusions by race/ethnicity or gender or sexual orientation. Those who are pregnant and/or currently use other tobacco products will not be excluded from participation, as they may benefit from vaping cessation.

### Inclusion criteria

1. English literacy;2. Age between 13-21 years; 3. Indicate they use social media “most” (≥ 4) days per week; 4. Have vaped at least once per week in the past 30 days; 5. Access to a computer or mobile phone with photo capability to verify abstinence from vaping; 6. Indicate they are considering quitting or are interested in quitting within the next 6 months; 7. Currently reside in California. This is because the funder for this study, the California Tobacco Related Diseases Research Program, requires the research be conducted in California. 

### Exclusion criteria

1. No English literacy; 2. Age under 13 or over 21 years; 3. Insufficient social media use (3 or fewer days per week); 4. Have not vaped at least once per week in past 30 days; 5. No access to computer or mobile phone with photo capability to verify abstinence from vaping; 6. Not interested in or considering quitting within the next 6 months; 7. Not California residents. 

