Before being able to proceed with the study, participants will indicate on an electronic form that they understand what this study is about, that their participation is voluntary, that they are not required to complete any part of this study, and that there are risks associated with study participation. Incomplete or incorrect answers will result in the potential participant being prompted to review the full consent document before attempting the consent questions again. Potential participants will not be enrolled in the study if they fail to complete the form four times. In both the screening and baseline survey, participants are asked about location questions (zip code in the screening and county in the baseline survey). Our research staff will check the consistency of their answers and contact the participants with inconsistent answers using the contact information they provided to confirm the authenticity of the participants. In addition, participants must follow the study account on Instagram, and study personnel will review the profiles of followers for consistency with age and California location. Irregular or inconsistent answers or participants otherwise having difficulty completing the form will be contacted by trained study personnel who will review the consent material and assist with study enrollment. Study personnel may detect behavior, responses or Instagram accounts that do not appear to be authentic. Fraudulent participants identified through this process will be removed and documented. In the consent form, participants will be asked to remain in the study’s Instagram group throughout the duration of the study (about 7 months) for the intervention and for follow-up contacts. Participants will be paid $10 in the form of an electronic gift card for completing the baseline assessment. Participants will be paid $15–35 for each follow-up assessment for a possible total of $100.

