
#### Intervention group

The vaping cessation intervention will be implemented on Instagram. Participants in the intervention group will be assigned to groups on Instagram, where they will receive up to 3 posts per weekday for 25 days (5 weekdays, no weekends) over 5 weeks. Posts incorporate skills from cognitive behavioral therapy, found effective for long-term smoking cessation [48], as well as the TTM processes of self-liberation (e.g., making a commitment to quit), stimulus control (e.g., removing vaping paraphernalia from the home), and counter conditioning (e.g., engaging in alternative behaviors). Posts also encourage setting a quit date and making a detailed quit plan. Posts include a combination of images, videos, and text to elicit a response from participants. Posts may suggest that participants use their social media or real social networks for support with vaping cessation. However, they are not required to share any information about substance use on social media.

Groups are facilitated by a trained Guide, a certified cessation counselor with over 4 years of experience facilitating smoking cessation groups on Facebook, working with the Principal Investigator and Sub-Investigators. The Guide will send the daily posts in groups. In addition, the study employs a pediatrician on demand if additional expertise or clinical advice is needed. Participants will be educated about signs of nicotine dependence and if they express interest in pharmacotherapy, we will encourage them to access this through their personal healthcare providers.

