### Data collection and management

The three follow-up assessments conducted immediately, 3 months, and 6 months after the treatment will be administered online using Qualtrics through UCSF MyAccess, which includes Secure Sockets Layer encryption, and adheres to HIPAA standards, allowing encrypted transmission of all survey data. Research staff will send emails, text messages, and messages in Instagram with the survey links to notify participants of assessments. At most three emails will be sent to remind participants of the assessments. Those who don't respond after the three contact attempts are counted as dropout at each time point. Those who don't respond in the previous assessments will still be contacted for later assessments. For instance, a participant who did not do the assessment at 3 months post-treatment will still be notified of the assessment at 6 months post-treatment up to three times. Survey data will be securely transferred to password-protected Excel or SPSS files that will be securely stored online using the UCSF Research Analysis Environment, a secure, HIPAA-compliant desktop environment. Files with identifying information will be stored separately from files with other forms of data. Data will only be accessed by the PI and a research assistant until it is de-identified. Study investigators have completed required UCSF training and certification in the conduct of research with human subjects. All collected data will be analyzed and reported in aggregate form for publications. All survey data collection and storage procedures are consistent with current HIPAA guidelines.

In order to ensure and maintain the scientific integrity of this human subject research project, and to protect the safety of its research participants, we will assemble a Data Safety Monitoring Board (DSMB). The DSMB will meet every six months via video conferencing to review the study protocol and procedures. The DSMB will have the responsibility of assuring that participants are not being exposed to unnecessary or unreasonable risks as a result of the pursuit of the study’s scientific objectives.

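### Eligibility counts use of any social media although treatment runs only on Instagram, and the Instagram and authenticity checks have no stated place before automatic randomisation

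*Protocol article*

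**What the plan says.** Item 3 of the Inclusion criteria reads "Indicate they use social media “most” (≥ 4) days per week", and item 3 of the Exclusion criteria mirrors it: "Insufficient social media use (3 or fewer days per week". Neither names a platform. The Recruitment section says that the website's eligibility questions address these lists.

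The Intervention group section states: "The vaping cessation intervention will be implemented on Instagram". Participants there receive up to 3 posts per weekday for 25 days over 5 weeks.

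Instagram enters as a condition only in the Study procedure section, among the checks on authenticity: "participants must follow the study account on Instagram, and study personnel will review the profiles of followers for consistency with age and California location". The same section compares the zip code given at screening with the county given in the baseline survey, and says that fraudulent participants found through this process are removed and documented. On consent it adds that "participants will be asked to remain in the study’s Instagram group throughout the duration of the study (about 7 months".

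The next paragraph of that section gives the sequence: consent, login, baseline assessment, then computer-generated assignment that happens automatically for those who complete baseline.

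**The concern.** The investigators chose to screen on how often people use social media, but applied the threshold to any platform and not to the one that carries the treatment. Someone who is on another platform daily and opens Instagram once a month passes. If allocated to the intervention, that person may see few of the posts while remaining in the randomised comparison. The Discussion itself notes that low engagement significantly reduced efficacy in earlier social media interventions.

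The second issue is order. If the follow step, the profile review or the location check is finished only after allocation, some randomised participants may be removed. Removal after allocation gives up part of the protection of randomisation. It can also fall unevenly on the two arms, because only the intervention arm needs Instagram for its treatment.

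**Working it through.** **Eligibility.** Three places, side by side:

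- Inclusion and Exclusion criteria, item 3: any social media, cut at 4 or more days a week.
- Study procedure: every participant must follow the study's Instagram account. Profiles are reviewed for age and California location, and staff look for accounts that do not seem authentic. No level of use is set.
- Intervention group: delivery on Instagram only.

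An Instagram account is thus a condition in practice, but regular use of it is not.

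**Order.** The county answer comes from the baseline survey, so the zip-versus-county check cannot be done before baseline is complete. Allocation follows baseline completion automatically, and no hold is described. The follow step and profile review have no stated place in the sequence. The statement about what must happen before a participant can proceed with the study concerns the consent-comprehension form, not the follow step. As written, all three checks can end after allocation.

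**Reproducing the stated sample size.** Inputs from Sample size estimation: α = 0.05 (taken as two-sided), power 0.80, rho = 0.43, p1 = 0.032, p2 = 0.083, 234 per group.

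For a single time point, with pooled variance:

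n = [1.96·√(2·p̄(1−p̄)) + 0.842·√(p1(1−p1) + p2(1−p2))]² / (p2−p1)²

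with p̄ = (0.032 + 0.083)/2 = 0.0575. This gives (0.645 + 0.275)²/0.051² ≈ 326.

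The repeated-measures factor under compound symmetry is (1 + (m−1)·rho)/m.

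- m = 2: (1 + 0.43)/2 = 0.715, giving 234, the stated figure.
- m = 3, the number of follow-ups in the Primary analysis: (1 + 0.86)/3 = 0.62, giving 203.

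**Illustrating dilution.** Suppose that a share f of the intervention arm has the control rate. The arm's rate is then 0.032 + 0.051·(1−f). Power with 234 per group is

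Φ{[d − 1.96·√(2·p̄(1−p̄)·k/234)] / √([p1(1−p1) + p2(1−p2)]·k/234)}

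where d is the diluted difference, p2 and p̄ take their diluted values, and k is 0.718 (set so that 234 gives exactly 80% at f = 0) or 0.62 (three time points).

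| f | Intervention rate | Power, stated 80% basis | Power, three time points |
|---|---|---|---|
| 0 | 8.3% | 80% | 85% |
| 5% | 8.0% | 77% | 83% |
| 10% | 7.8% | 73% | 79% |

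Worked case, f = 10%, k = 0.718: d = 0.0459; (0.0459 − 0.0350)/0.0178 ≈ 0.61; Φ(0.61) ≈ 0.73.

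The shares f are assumptions. The article gives no share of infrequent Instagram users among those who would enrol.

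**The case against.** A reader might infer that people who never use Instagram can join. The Study procedure section does not support this: everyone must follow the study account, staff review profiles, and accounts that look inauthentic are followed up. An account could still be opened just for the study, but total non-use is not let through unchecked.

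A reader might also infer that study contact depends on Instagram. It does not: "Research staff will send emails, text messages, and messages in Instagram with the survey links to notify participants of assessments". Reminders go by email, and Data analysis also names email for re-contact.

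It is tempting to take the Background figure, "being used by 72% of adolescents in 2018", subtract it from 100%, and assume that 28% of the arm goes untreated, which would put power at about 57% (64% with three time points). That figure describes adolescents in general. It does not describe people aged 13 to 21 who already use social media on most days, agree to join an Instagram group and follow the account.

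Three further points stand. The 8.3% is the rate in the whole intervention group of the earlier Facebook trial, so some non-engagement may already be in it. The model gives infrequent users no benefit at all, which the article does not say. Broad eligibility is also a legitimate choice if the aim is the effect of offering the programme, although the Objectives speak of efficacy.

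On order, Fig. 1 is not shown and the full protocol may place the checks before allocation. The follow and removal rules also make no distinction by arm. Uneven removal is therefore a possibility and not a stated feature. What remains is that the text describes automatic allocation on baseline completion alongside a check that needs baseline answers, with no hold between them.

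**Conclusion.** The concern holds in a limited form. The eligibility lists do not carry the Instagram condition that the Study procedure section imposes, and no part of the article asks for regular Instagram use, so infrequent users can enrol. The loss of power is a risk of unknown size: about 3 to 7 percentage points if 5% to 10% of the intervention arm got no benefit, from a start of 80% on the stated basis (about 2 to 6 points from 85% with three time points). These figures rest on the assumed shares and on zero benefit for those participants. They do not show that the trial is underpowered, and the stated sample size itself reproduces.

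The order of checks is the firmer part, because it follows from the text without any assumed share: as written, participants can be removed after allocation. The article does not show that this would happen often or differ between arms.

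**What to change.** 1. Add to inclusion criterion 3, with a matching exclusion and screener question, that the person has an active Instagram account in regular use. Whether to set a frequency cut-off, and where, is the sponsor's choice; the documents do not settle it.
2. State in the Study procedure section that the automatic allocation is released only after the follow step, the profile review and the zip-versus-county check are complete, in the same way for every participant and before the arm is known.

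This costs one screener question and one reordered step on the enrolment website. The eligible pool becomes slightly smaller, there is a short wait between baseline and allocation, and the result applies to Instagram users.
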